#### Strategies to improve adherence to interventions {11c}

Retention during the intervention and maintenance periods will be handled by the coaches (e.g., coach will attempt to contact participants via their preferred contact method and reschedule missed sessions when possible). The study staff will also send quarterly study newsletters and birthday and holiday cards to participants throughout the study.

#### Relevant concomitant care permitted or prohibited during the trial {11d)

For the intervention period (weeks 1–8), we will use a constrained usual care model (requesting participants to keep antihypertensive medications constant if possible) to reduce non-study-related variability in the acute intervention phase. For the maintenance and no intervention periods (months 2–12), we will track the medication changes at study assessments but will not require participants to remain at a consistent dose. This plan is based upon current hypertension guidelines that allow for lifestyle interventions for 3–6 months in elevated/stage I hypertension. Both groups will receive written instructions reminding them to follow up as recommended with primary care.

#### Provisions for post-trial care {30}

This trial does not include provisions for post-trial care. If participants inquire about additional sleep interventions after the trial, they will be provided with information about local sleep centers.

### Outcomes {12}

Study outcomes and assessment time points are listed in Fig. 2.

Primary outcome: The primary outcome is a change in sleep duration from baseline to 8 weeks. Sleep duration at baseline and 8 weeks will each be calculated as averages over 10-day periods. Sleep duration will be measured by 8–10 days of actigraphy at baseline/screening, week 8, and 6 and 12 months with the Actiwatch Spectrum device (Philips Respironics Inc.). Devices will be configured using default settings and scored using the Acitware Software (Philips Respironics, Inc.). Actigraphy will be manually scored using a standardized procedure [16].

Main secondary outcome: The main secondary outcome will be change in 24-h SBP from baseline to 8 weeks. This measure will be calculated as an average for the 24-h period at baseline and 8 weeks. BP will be assessed by 24-h ABPM at home using the Spacelabs ambulatory BP monitor (Spacelabs Healthcare, Hertford, UK). Participants will wear the BP monitor at baseline/screening, week 8, and 6 and 12 months. Monitors will be programmed to take readings in random 20-min intervals during the day and 30-min intervals at night.

Other secondary outcomes: Changes from baseline to 6 months and from baseline to 12 months will be measured to evaluate the maintenance of sleep duration changes. In addition, changes in 24-h SBP from baseline to 6 and 12 months will be measured to evaluate the maintenance. We will also measure the change in 24-h diastolic blood pressure (DBP) from baseline to 8 weeks and 6 and 12 months. We will measure diet quality by administering the Automated Self-Administered 24-h Dietary Assessment Tool and calculating the Healthy Eating Index (HEI-2018) [17], a composite measure derived from the 24-h recall measurement that uses food groups and nutrients collected in the diet recall to compute the US dietary guidelines into a single measure. Changes in the HEI reflect the overall change in the healthfulness of diet. We will also compute macronutrients and key food group/diet behaviors (e.g., fast food, fruit/vegetable intake) from the ASA-24 data for use in exploratory analysis.

Objective 24-h physical activity data including sedentary behavior will be collected using the ActivPAL4 activity monitor [18, 19]. The main measure of interest will be minutes of moderate and vigorous physical activity per day (MVPA).

Other measures of cardiometabolic risk will be measured at screening, week 8, and months 6 and 12 including BMI and body fat estimation using a bioimpedance scale (Tanita of America), waist and hip circumference, lipids, and HbA1c. We will also evaluate the effects on nocturnal and diurnal BP and on non-dipping BP status defined by ABPM levels as mean nighttime to daytime SBP/DBP ratio of > 0.90.

Participants will complete measures of patient-reported outcomes at session baseline, week 8, and months 3, 6, 9, and 12, including the PROMIS sleep disturbance, sleep-related impairment and sleepiness [20], and mood [21].

We will assess the intervention acceptability and user engagement to inform our findings and plan for future studies (Fitbit usage, coaching session attendance and duration, and email lesson engagement and use surveys and open-ended questions at the end of the intervention and follow-up periods).

### Participant timeline {13}

A description of the participant timeline is listed in Fig. 4.

**Fig. 4 Fig4:**
[figure not shown]
A description of the participant timeline

### Sample size {14}

Our power calculations are based on the assumption that the standard deviation (SD) for change in sleep duration from baseline to 8 weeks will not exceed 37.4 min, which is 10% higher than the SD for change in sleep duration of 34 min reported after 40 days in our previous study [22]. We also assume the Pearson correlation between baseline and follow-up sleep duration will not exceed 0.75, and that the attrition rate will not exceed 20%. Under these assumptions, 120 randomized participants (60 in each of the treatment and control groups) will provide at least 80% power with 2-sided *α* = 0.05 to detect a treatment effect of 20.2 min.

If we also assume that (1) the SD for baseline SBP will be $$\le$$ 11.8 mmHg, which is 10% higher than the average baseline SD reported in two previous studies [refs]; (2) the Pearson correlation between the baseline and 8-week follow-up SBP values will be $$\ge$$ 0.70; and (3) the attrition will be $$\le$$ 20%, and the sample size of 60 patients per treatment group will additionally ensure at least 80% power for the main secondary analysis to detect a treatment effect on the change in SBP of 4.86 mmHg.

### Recruitment {15}

The study will use both active and passive recruitment methods. For active recruitment, patients from the University of Utah Health (UU Health) primary care practices who meet the initial criteria (age, BP) will be sent letters explaining the study and providing information for online screening. The study staff will follow-up letters with a phone call and email to potential participants. We will work with local community leaders and community health workers to enhance the recruitment of diverse study participants, such as providing flyers and information about the study to share with their communities. We will attend local health fairs and conduct BP screening and share study information for interested participants. For passive methods, we will post flyers on the University of Utah campus and nearby areas (e.g., grocery stores and coffee houses) and will post ads on social media (e.g., Facebook). If recruitment slowdowns happen, the team could send more letters, expand to a larger number of clinics, post more frequently on social media, consider in-person recruitment in primary care visits, and attend more health fair events.

### Assignment of interventions: allocation

#### Sequence generation {16a}

Randomization will be performed using random permuted blocks with stratification by sex and antihypertensive medication use.

#### Concealment mechanism {16b}

The randomization allocation will be completed by the biostatistician and loaded into the REDCap system, where it will be concealed from the study investigators and staff.

#### Implementation {16c}

After the screening is completed, the study staff will enter data into a REDCap form including the inclusion/exclusion criteria and stratification information. The interventionist only will have access to the randomization module in REDCap and will complete the randomization and notify the participant of his or her assignment.

### Assignment of interventions: blinding

#### Who will be blinded {17a}

The study staff, the PI, and the co-Is who are not directly responsible for delivering the intervention will be blinded. Participants and the interventionist will be unblinded. The interventionist will not be involved in the collection of outcome measures. The statistician, who creates the randomization table and is completing the analyses will also be unblinded.

#### Procedure for unblinding if needed {17b}

The study has appointed an independent safety monitor, a primary care physician, who is unaffiliated with the study and is available to review the adverse events. He will be unblinded if necessary and will recommend to the study team if a situation arises that unblinding is critical to addressing the situation.

### Data collection and management

#### Plans for assessment and collection of outcomes {18a}

##### Screening measures

Participants will complete self-report measures to evaluate for the presence of elevated depressive symptoms and symptoms of common sleep disorders on the web/phone prescreening. Participants who demonstrate elevated depressive symptoms (score ≥ 15) on the PHQ-8, moderate severity of restless legs (score ≥ 11) on the International Restless Legs Working Group Questionnaire, or severe insomnia on the Insomnia Severity Index [23] and scores ≥ 3 on the STOP questionnaire [24] will be excluded. At the baseline/screening visit (visit 1), participants who are at risk for OSA (STOP = 2) will complete one night with the Apnea Link monitor (Resmed, Inc.) to screen for the presence of obstructive sleep apnea. Participants who have moderate severity or greater OSA (Apnea Hypopnea Index ≥ 15) will be excluded from the study. They will be mailed a notification letter with screening results recommending they discuss the results with their provider.

##### Outcome measures

Primary outcome: Sleep duration at 8 weeks. Sleep will be measured by 8–10 days of actigraphy at baseline/screening, week 8, and 6 and 12 months with the Actiwatch Spectrum device (Philips Respironics Inc.). Devices will be configured using default settings and scored using the Acitware Software (Philips Respironics, Inc.). Actigraphy will be manually scored using a standardized procedure [16]. Participants will be provided with verbal and written instructions. Participants will wear the Actiwatches for 8–10 days in order to maximize the possibility of collecting 7 nights. Data will be considered valid if there are at least 5 nights. After the watches are retrieved, the research staff will use the Actiware software program to calculate the following variables: total sleep time, sleep onset time, sleep offset time, sleep duration, sleep efficiency, sleep latency, wake after sleep onset, and sleep fragmentation index. The staff will be trained on the scoring of actigraphy using a standardized procedure of readings, hands on practice/demonstration, and recorded presentations. Scored of each study file is reviewed by study PI [name] for scoring quality.

Main secondary outcome: 24-h SBP at 8 weeks. We will use the validated (AAMI criteria) SpaceLabs 90,207 monitor which is generally considered the “gold standard” for ABPM [25, 26]. ABPM for 24 h will be conducted at baseline/screening, 8 weeks, and 6 and 12 months follow-up. At each of the three 24-h ABPM assessments, the proper BP cuff size will be determined by measuring each participant’s arm circumference at the mid-point between the acromion and olecranon. Next, the monitor will be initialized, and the participant will be fitted with a SpaceLabs 90,207 monitor. Participants are instructed to hold their arm still (by their side or with their forearm resting on a desk/table when seated) when a reading is being taken. Each participant will be instructed by the study coordinator to try to keep their arm still and in the neutral position (which will be demonstrated for the participant prior to leaving the visit) from the time that she or he feels the arm cuff begin to inflate until it is fully deflated. The study staff is trained on ABPM procedures by 1:1 demonstration and practice with [name], study co-I. After demonstrating the ability to place the ABPM and instruct participants appropriately, the staff members are approved to conduct this study assessment.

Dietary intake will be collected using the ASA-24, an online automated 24-h dietary recall system [27]. The main measure of diet quality will the HEI-2018 [28], a composite measure that uses food groups and nutrients collected in diet recall to compute the US dietary guidelines into a single measure. Changes in the HEI reflect the overall change in the healthfulness of diet. We will also compute macronutrients and key food group/diet behaviors (e.g., fast food, fruit/vegetable intake) from the ASA-24 data for use in exploratory analysis.

Objective 24-h physical activity data including sedentary behavior will be collected using the ActivPAL4 activity monitor [18, 19]. This miniature electronic logger is validated to classify time spent lying, sitting, standing, and intensity of physical activity. The device is placed in a waterproof cover and taped to the participants’ middle anterior aspect of the upper thigh, thus avoiding the need to change accelerometer placement when changing clothes. A picture will be drawn on the waterproof cover to depict the correct orientation of the device. Data will be processed and analyzed using the ActivPAL software according to standardized procedures and best practices [29, 30]. In order to be considered valid data, participants must have 5 days with at least 23 h per day. We are using separate devices for sleep and physical activity because hip/thigh vs. wrist placement is important for measurement of physical activity and sleep [31, 32].

Other measures of cardiometabolic risk will be measured at screening, week 8, and months 6 and 12 including BMI and body fat estimation using a bioimpedance scale (Tanita of America, Arlington Heights, IL), waist and hip circumference, inflammation (IL-6, CRP), lipids, and HbA1c. Training procedures for body measurements include 1:1 training and practice with [name] and sign off when the staff member can demonstrate following procedures. We will also evaluate the effects on nocturnal and diurnal BP and on non-dipping BP status defined by ABPM levels as mean nighttime to daytime SBP/DBP ratio of > 0.90 [33].

Participants will complete measures of patient-reported outcomes at session baseline, week 8, and months 3, 6, 9, and 12, including the PROMIS sleep disturbance and sleep-related impairment [20], sleepiness [34], and mood [21]. The PROMIS sleep disturbance and sleep-related impairment demonstrate strong internal consistency and have been validated to a mean of 50 and SD of 10 points [20]. The Epworth Sleepiness Scale [35] is a measure commonly used in clinical practice for sleep disorders. The Patient Health Questionnaire, 8-item measure [21] is highly correlated with clinical diagnoses of depression, with scores > 10 associated with elevated depression.

We will assess intervention acceptability and user engagement to inform our findings and plan for future studies (Fitbit usage, coaching session attendance and duration, and email lesson engagement and use surveys and open-ended questions at the end of the intervention and follow-up periods).

Data collection forms are not posted publicly but will be made available upon request.

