## Statistical methods

### Statistical methods for primary and secondary outcomes {20a}

The primary outcome of the proposed study is the change in the mean sleep duration from baseline to 8 weeks. The study sample size has been determined based on the primary analysis of covariance (ANCOVA) that will compare mean sleep duration at 8 weeks, with statistical adjustment for the baseline sleep duration and the sex and age randomization strata. The proposed ANCOVA approach is recommended for the evaluation of treatment effects on continuous outcomes in randomized trials because it optimally accounts for random imbalances in the outcome at baseline and regression to the mean, thus providing superior statistical power compared to the analyses of change scores or follow-up scores without adjustment for baseline levels [36].

The main secondary outcome for this study is the change in SBP from baseline to 8 weeks. Evaluation of the 24-h SBP outcome at 8 weeks will assure that few patients will have modified their antihypertensive medication regimen over the 8-week interval prior to the primary outcome assessment.

Evaluation of the 24-h SBP outcome at 8 weeks will assure that few patients will have modified their antihypertensive medication regimen over the 8-week interval prior to the primary outcome assessment. Similar ANCOVA models as used with sleep duration will also be used to evaluate the acute effects on this and other numeric secondary and tertiary outcomes.

We will use linear mixed models [37, 38] to analyze changes in sleep duration, BP measures, sleep, and other numeric tertiary outcomes over all follow-up visits, including the 8-week and 24-week assessments. These analyses will evaluate the persistence of treatment effects over the full 24-week follow-up period and will allow us to utilize all data collected (i.e., baseline, 8 weeks, and 24 weeks) while allowing for within-subject variation.

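### Dipping is named as an outcome only as a yes/no status; testing the continuous night/day ratio from the same recordings would gain power at almost no cost (minor)

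*Protocol article*

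**What the plan says.** Two places in the protocol article define the outcome. Outcomes {12} states "We will also evaluate the effects on nocturnal and diurnal BP and on non-dipping BP status defined by ABPM levels", and the Outcome measures part of section {18a} repeats this with the same cut, "non-dipping BP status defined by ABPM levels as mean nighttime to daytime SBP/DBP ratio of > 0.90". In both, the night/day ratio appears only as the quantity that is cut. Neither lists the ratio itself, or the percentage dip, as an outcome. Both list nocturnal and diurnal BP in the same sentence.

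Statistical methods {20a} makes baseline-adjusted ANCOVA the primary method and justifies it by its gain in power. It then extends it to the remaining numeric outcomes: "Similar ANCOVA models as used with sleep duration will also be used to evaluate the acute effects on this and other numeric secondary and tertiary". Linear mixed models are planned for BP measures and other numeric outcomes across visits. The section names no model for a binary outcome.

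Sample size {14} covers sleep duration and SBP only. It gives no SD, correlation, expected effect or prevalence for dipping.

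**The concern.** The night/day ratio is a continuous quantity that every 24-hour recording already yields. Cutting it at 0.90 discards how far each participant moved. Someone going from 0.89 to 0.91 counts as a complete change of state, while someone going from 1.02 to 0.92 counts as no change. The status also falls outside the numeric-outcome models that {20a} prefers for their efficiency, whereas the ratio would fit them directly.

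The article cites a source for the definition of non-dipping but gives no reason why the treatment effect has to be tested on the cut. What is at stake is limited but real: a null result on non-dipping status could come from a test much weaker than the recordings allow.

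**Working it through.** **1. Number analysed, and the plan's own figure.** The plan has "120 randomized participants (60 in each of the treatment and control groups") and assumes "the attrition rate will not exceed 20" per cent, so 60 × 0.8 = 48 per arm. For sleep, the inputs are "standard deviation (SD) for change in sleep duration from baseline to 8 weeks will not exceed 37.4 min" and "Pearson correlation between baseline and follow-up sleep duration will not exceed 0.75":
- SD at one time point = 37.4 / √(2 × (1 − 0.75)) = 52.89 min
- ANCOVA residual SD = 52.89 × √(1 − 0.75²) = 34.98 min
- detectable effect at 80% power = 2.80 × 34.98 × √(2/48) = 20.0 min (normal approximation), or 20.2 min with the t distribution

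This reproduces "at least 80% power with 2-sided *α* = 0.05 to detect a treatment effect of 20.2 min". The SBP figure also reproduces: residual SD 11.8 × √(1 − 0.70²) = 8.43 mmHg, and detectable effect 4.82 (normal) or 4.87 (t) against the stated 4.86 mmHg. So 48 per arm is the right base. The plan has no figure for dipping to reproduce.

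**2. Assumptions for the ratio (none is in the document).** The ratio is normal. The baseline to follow-up correlation r is 0.3, 0.5 or 0.7. The control-arm share above 0.90, p0, is 30% or 50%. Two-sided alpha is 0.05. The effect, in SD units of the ratio, is first set where ANCOVA has about 80% power: d = 2.83 × √((1 − r²) × 2/48), which gives 0.55, 0.50 and 0.41 for r = 0.3, 0.5 and 0.7.

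**3. One case by hand (r = 0.5, p0 = 30%, normal-approximation d = 0.495).** The cut lies 0.524 SD above the control mean, so the share above it in the intervention arm is 1 − Φ(0.524 + 0.495) = 15.4%. For an unadjusted comparison of 30% with 15.4%, the mean share is 22.7%:
- critical difference = 1.96 × √(2 × 0.227 × 0.773/48) = 0.168
- SE under the alternative = √((0.30 × 0.70 + 0.154 × 0.846)/48) = 0.084
- power = Φ((0.146 − 0.168)/0.084), about 40%, against 80% for ANCOVA on the ratio

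**4. Simulation, 1,500 trials per case.** The status is analysed by logistic regression adjusted for the continuous baseline ratio.

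| r | p0 | ANCOVA on ratio | Logistic on status | Loss (points) |
|---|---|---|---|---|
| 0.3 | 30% | 79.2% | 45.6% | 33.6 |
| 0.3 | 50% | 76.9% | 55.2% | 21.7 |
| 0.5 | 30% | 80.4% | 47.1% | 33.3 |
| 0.5 | 50% | 78.6% | 55.6% | 23.0 |
| 0.7 | 30% | 80.1% | 38.0% | 42.1 |
| 0.7 | 50% | 77.9% | 46.6% | 31.3 |

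Adjusting for baseline status instead of the baseline ratio is somewhat worse. At r = 0.7 and p0 = 30%, power is 34.8%, a loss of 45.3 points.

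**5. Smaller effects.** In the same cases with 800 trials each, the loss is about 8 to 16 points at half the effect, where ANCOVA itself has about 30% power. At a quarter of the effect it is about 2 to 5 points, where ANCOVA has about 11%.

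**The case against.** The strongest reply has four parts.

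- **The size rests on chosen inputs.** The document gives none for the ratio, and the effect size matters most. Fixing it where ANCOVA has 80% power produces the largest figures shown. A reader might infer that the plan forfeits a fixed 20 to 40 points. It does not support that, because nothing in it says the true effect is that large. This part stands, so the loss is given as conditional and at more than one effect size.
- **The binary test is supplied here.** The article names none, and an analysis plan that is not shown may specify one or may add the continuous ratio. This also stands. The article does not exclude the ratio, and a missing test for a minor binary outcome is not itself a fault. What remains is that the article states its dipping outcome twice, both times as the status.
- **Nocturnal and diurnal BP are evaluated in the same sentence.** They are numeric and fall under the ANCOVA and mixed models. A reader might infer that continuous night-time information is lost. It is not, and those results would sit beside a null on status. They still do not test the ratio: both levels can fall together with no change in dipping.
- **A prevalence is a legitimate target, and dipping is a minor measure.** That is true and is why the point is minor. The prevalence can still be reported.

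**Conclusion.** The point holds as a minor improvement. The protocol article names dipping as an outcome only in dichotomised form, and testing only that form is less efficient than testing the ratio. With 48 completers per arm, a normal ratio, correlation 0.3 to 0.7 and control prevalence 30% to 50%, baseline-adjusted logistic regression loses about 20 to 40 points at the effect where ANCOVA has 80% power, and about 8 to 16 points at half that effect. The loss becomes small when the effect is so small that neither analysis has useful power.

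It would go too far to conclude that the trial is underpowered or that a planned conclusion fails. Dipping is one of several additional cardiometabolic measures and carries no power claim. The sample size, the sleep-duration analysis and the 24-hour SBP analysis are unaffected.

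**What to change.** In Outcomes {12} and in Outcome measures under {18a}, name the continuous night/day SBP ratio as the tested dipping outcome, with the night/day DBP ratio as a separate supportive outcome. State that each is analysed at 8 weeks by the ANCOVA of {20a}, adjusted for its own baseline ratio, and at later visits by the same linear mixed model. Keep the proportion of participants with a ratio above 0.90, by arm, as a descriptive summary.

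The change takes about a sentence in each place and needs no new data, visits or participants. It has two costs. The tested result becomes a difference in ratio, which is less familiar clinically than a prevalence, and the separate DBP ratio adds one secondary test.
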